Findings from our first study suggest that “Thursdays at the Museum” may improve older adults’ mental (i.e., well-being and quality of life) and physical (i.e., frailty) health. The relationship between well-being, quality of life, and physical health is complex. Previous studies, including our first study, suggested the existence of a chronological sequence of benefits: positive experiences induced by art-based activities improve well-being, which improves quality of life and, finally, physical health [6–13, 21]. This sequence may explain the changes in outcomes over time reported in our first study. However, the changes in well-being, quality of life, and physical health that older community dwellers experience over time and independently of any intervention are sparsely known. These aging-related changes may influence the effects specific to “Thursdays at the Museum.” We hypothesize that changes in well-being, quality of life, and frailty due to older community dwellers’ participation in “Thursdays at the Museum” (1) each have not the same profile of evolution over time; (2) are greater than those observed with aging (i.e., experienced by the older adults with or without morbidities that make up the control group); (3) are improvements of well-being, quality of life, and frailty; and (4) may persist after the discontinuation of “Thursdays at the Museum.”

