### Outcomes

The primary outcome is the change in WEMWBS score between the baseline assessment (M0) and the end of the 3-month cycle (M3), calculated using the formula ((score M^*n* + 1^ – score M^*n*^)/((score M^*n* + 1^ + score M^*n*^)/2)) × 100 [21, 26], expressed in percentage. Mean values and standard deviations will be used to define quantitative variables. The secondary outcomes are (1) the changes in WEMWBS scores between M0 and M1, M0 and M2, M0 and M9, and M0 and M15; (2) the mean WEMWBS scores before and after workshops in the intervention group at M0, M1, M2, and M3; (3) the changes in CESAM scores and its distribution of frailty categories (vigorous versus mild, moderate, and severe frailty) between M0 and M1, M0 and M2, M0 and M3, M0 and M9, and M0 and M15 [23]; (4) the change in EQ-5D scores, including VAS scores, between M0 and M1, M0 and M2, M0 and M3, M0 and M9, and M0 and M15 [25]; (5) the frequency of planned and unplanned physician visits, ER visits, and hospital admissions at M1, M2, M3, M9, and M15 [14, 16]; and (6) the changes in mean values of heart rate, daily steps, an sleep duration, and sleep phases, expressed in percentages, between M0 and M1, M0 and M2, and M0 and M3 for the subset of participants with recordings of these physiological measures. All changes will be expressed in percentages as mean values and standard deviations.

The number of workshops attended during the 3-month cycle of intervention is used to assess compliance with the participatory art-based activity. Compliance is defined as having attended at least 10 (83.3%) of the 12 workshops. If a participant attends a workshop for at least 1 h, they are considered to have attended a full workshop. If not, they are recorded as absent.

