### Data analysis

Analyses will be performed (1) with the intention to treat for all enrolled participants randomized into two groups (i.e., intervention versus control) and (2) per protocol (i.e., removing data from participants who were not compliant with the protocol) for participants who will be entirely assessed through an 83.3% (i.e., participants who attended 10 on 12 workshops) compliance to the intervention. Analyses will be done through the SPSS Software (version 23.0; SPSS, Inc., Chicago, IL). Missing data will be taken into account with regression imputation. Data will be imputed only if the percentage of participants with missing data is under 10%. The continuous variables’ distributions will be studied (mean, median, mode, minimum, maximum, confidence interval around mean, standard deviation). For the categorical variables, frequencies will be calculated. First, the participants’ baseline characteristics (age, sex, etc.) will be described for each group and compared (i.e., intervention versus control) using parametric and non-parametric tests according to variables’ distribution. Pearson’s chi-square tests (or Fisher’s exact tests) will be used for qualitative variables. For quantitative variables, the statistical tests used will be unpaired *t* tests or non-parametric Mann-Whitney *U* tests for comparing 2 groups, as appropriate.

Second, group comparisons of changes (i.e., ((score M^*n* + 1^ – score M^*n*^)/((score M^*n* + 1^ + score M^*n*^)/2)) × 100) in outcome values between M0 and M1, M0 and M2, M0 and M3, M0 and M9, and M0 and M15 will be performed using repeated measures tests as appropriate. The global significance limit will be set at 0.05 and all tests will be bilateral. In addition to this univariate analysis, a multivariate analysis will be performed to determine the effect of the intervention while adjusting for age, sex, number of medications taken daily, and CPQ score. These adjusted variables are covariates that may influence the relationship between outcome measures (i.e., well-being, quality of life, and frailty) and the participatory art-based activity intervention.

Third, to identify the outcomes with the highest magnitudes of change (i.e., greater effect attributable to the intervention), we will graph the mean difference of each outcome that is significantly different when comparing intervention group participants to those in the control group. Results will be presented as forest plots.

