Fourth, analysis of compliance criteria will be based on between-group comparisons using, for quantitative variables, parametric and non-parametric tests according to variables’ distributions, and, for qualitative variables, Pearson Chi-square tests.

An intermediate analysis will be carried out with the first 90 participants. It will focus on the primary evaluation criterion and consider a *p* value < 0.001 sufficiently significant to stop the study.

The final analysis of the primary evaluation criterion in all 150 patients will consider the value *p* < 0.0498 as significant (Haybittle-Peto method).

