## Discussion

*Art is good for your health* is a frequently encountered mantra in mainstream media, reflecting the growing amount of published evidence regarding art-based activities’ positive effects on health and well-being. Unfortunately, there is a lack of robust data based on gold-standard experimental study designs like RCTs. Furthermore, this advice is applicable to mental health (i.e., well-being and quality of life) in the elderly population but must still be validated for older community dwellers’ physical health condition. Nascent research and action in the field of health prevention and promotion using art-based interventions highlight the key role museums will play as partners in health policy [8, 17–19]. The MMFA is a Canadian leader in this field, partnering with health professionals and researchers. With the A-Health RCT, we have a unique opportunity to demonstrate that an art-based activity like “Thursdays at the Museum” is beneficial to both the mental and physical health of Montreal’s older community dwellers.

The use of art-based activities to improve mental and physical health is not a new concept, as exemplified by the art therapy field’s therapeutic application of art-making [4, 5, 7]. Art therapy is a non-pharmacological approach to improving well-being and quality of life used in patients with cancer, neuropsychiatric diseases, and physical disabilities [7]. In the past decade, the field of art therapy has undergone a shift toward novel application art-based activities, benefiting individuals other than patients with obvious health and wellness needs and expanding settings to include museums [8, 19].

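### The 0.05 limit is not made to hold across the secondary outcomes and visits, and only significant outcomes are plotted, yet the frailty and quality-of-life claims rest on them

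*Protocol article*

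**What the plan says.** **Primary outcome.** The Outcomes section names one: "The primary outcome is the change in WEMWBS score between the baseline assessment (M0) and the end of the 3-month cycle (M3"). The Data analysis section gives error levels for this criterion alone: p < 0.001 at an interim look after 90 participants, then p < 0.0498 at the end, in the sentence that begins "The final analysis of the primary evaluation criterion in all 150 patients will consider the value".

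**Secondary outcomes.** The same Outcomes section lists "the changes in WEMWBS scores between M0 and M1, M0 and M2, M0 and M9, and M0 and M15", then CESAM score, frailty category, EQ-5D score and VAS at all five follow-up times (the frailty and EQ-5D items meet at "between M0 and M1, M0 and M2, M0 and M3, M0 and M9, and M0 and M15 [23]; (4) the change in EQ-5D scores, including"). Three kinds of health-care use follow at five times, and the Fitbit measures at three.

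**Testing rule.** Changes from M0 to each later time are compared between arms by repeated measures tests, whose form is left open. The level is then set: "The global significance limit will be set at 0.05 and all tests will be bilateral".

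**Display rule.** The third analysis step sets out to find the outcomes with the largest changes attributable to the intervention. It does so by graphing, in forest plots, the mean differences of those outcomes that differ significantly between arms.

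**Claims.** The third hypothesis in the Background is that the changes "are improvements of well-being, quality of life, and frailty". The Discussion describes the trial as an opportunity to demonstrate that the activity "is beneficial to both the mental and physical health of" older community dwellers in Montreal. The Objective equates physical health with frailty, which the Outcomes section lists only as secondary.

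**The concern.** A limit called global suggests that 0.05 is the error rate for the whole set of tests. Nothing in the section brings that about for the secondary outcomes: there is no order of testing, no division of alpha, no condition on the primary result and no exploratory label. Yet the claims about physical health and quality of life can come only from those outcomes.

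The forest-plot rule makes this more than missing detail. It makes significance the condition for being shown as an effect of the intervention, so a chance result is displayed and its null neighbours are left out. Estimates selected in this way also tend to exaggerate the effect. The Discussion expects the results to inform health policy, so an unsupported statement that the programme improves frailty would have consequences.

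**Working it through.** **Benchmark.** One two-sided test at 0.05 has a false-positive chance of 0.05, or 0.025 in the direction favouring the intervention.

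**Step 1: count the between-arm comparisons in the Outcomes section.**

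| Secondary outcome | Measures × times | Contrasts |
|---|---|---|
| WEMWBS (M1, M2, M9, M15) | 1 × 4 | 4 |
| CESAM score and frailty category | 2 × 5 | 10 |
| EQ-5D score and VAS | 2 × 5 | 10 |
| Physician visits, ER visits, admissions | 3 × 5 | 15 |
| Heart rate, steps, sleep duration, sleep phases | 4 × 3 | 12 |
| Total | | 51 |

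The item "the mean WEMWBS scores before and after workshops in the intervention group at M0, M1, M2, and M3" concerns one arm and adds no between-arm contrast. Without health-care use, which is a frequency and not a percentage change, the count is 51 − 15 = 36. With one overall repeated-measures test per outcome there are 2 + 2 + 3 + 4 = 11 tests, or 12 with WEMWBS.

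**Step 2: isolate the tests behind the frailty and quality-of-life claims.** These are CESAM score, frailty category, EQ-5D score and VAS: 4 × 5 = 20 contrasts if each time is tested, or 4 tests if each measure has one overall test.

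**Step 3: chance of at least one false positive, all nulls true.**

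For m independent tests:
- Either direction: 1 − 0.95^m. For m = 20 this is 0.642; for m = 4 it is 0.185.
- Favourable direction: 1 − 0.975^m. For m = 20 this is 0.397; for m = 4 it is 0.096.

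For m normal statistics with common correlation ρ, let U be standard normal and c = 1.96:
- Either direction: 1 − E[{Φ((c − √ρ U)/√(1 − ρ)) − Φ((−c − √ρ U)/√(1 − ρ))}^m].
- Favourable direction: the same without the second Φ term.

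The documents give no correlations, so ρ is an assumption and a range is shown.

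| Tests | Direction | ρ = 0 | ρ = 0.5 | ρ = 0.8 |
|---|---|---|---|---|
| 20 contrasts | either | 0.64 | 0.42 | 0.22 |
| 20 contrasts | favourable | 0.40 | 0.21 | 0.11 |
| 4 overall tests | either | 0.19 | 0.16 | 0.11 |
| 4 overall tests | favourable | 0.10 | 0.08 | 0.06 |

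**Step 4: check with a less uniform correlation.** For the 20 contrasts, a simulation with correlation 0.3 to 0.7 across times and 0 to 0.5 across measures gives 0.41 to 0.61 in either direction and 0.21 to 0.36 favourable. These lie inside the ranges above.

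**Step 5: compare with the benchmark.** The smallest ratios are 0.114/0.05 = 2.3 (either direction) and 0.057/0.025 = 2.3 (favourable), both for four overall tests at ρ = 0.8. For 20 contrasts the smallest are 0.224/0.05 = 4.5 and 0.112/0.025 = 4.5.

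The counts leave out the repetition of analyses by intention to treat and per protocol, and with and without covariate adjustment.

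**The case against.** The best defence is that this is a condensed article. Multiplicity rules for secondary outcomes are commonly left to the full protocol or analysis plan, and the article does fix one primary outcome, a sample size based on it and an alpha rule for it. That stands: the primary conclusion is unaffected, and the absence of a hierarchy would not by itself be a finding. It does not answer what the article does state: a global 0.05 with no means of achieving it, and a plot limited to significant outcomes.

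Three stronger readings are tempting, and the text does not support them.

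- *At least 51 tests, each at 0.05.* The article never says that the level applies to each test, and repeated measures tests can mean one test per outcome. Fifty-one is the count under contrast-by-contrast testing, not a minimum.
- *A chance claim of benefit is likely.* In the favourable direction the chance for frailty or quality of life stays at or below 0.40 in every case computed. The two-sided figures also count results that favour control.
- *One small p-value will be claimed as benefit even if the primary test fails.* No sentence says so. Speaking of an opportunity to demonstrate benefit states an aim, not a decision rule, and persistence is hypothesised only as something that may occur. The forest-plot rule is the nearest the text comes.

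**Conclusion.** The point holds in a limited form. The 0.05 limit is not made to hold across the secondary outcomes, and the plan selects outcomes for display by significance, while two of the trial's three main claims rest on those outcomes. The false-positive risk for frailty or quality of life is materially inflated. If each time is tested separately it is at least about 4.5 times the single-test rate; with one overall test per measure it is about 2 to 4 times that rate. These figures assume that all nulls are true, that the test statistics are normal and that their correlation lies between 0 and 0.8. The size therefore depends on the assumed correlation and on which form of repeated measures test is meant; the direction does not. The error control of the primary comparison is not in question here. The change should be made, but the trial is not invalid without it.

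**What to change.** In the Data analysis section, after the sentence that sets 0.05:

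1. State that the M0 to M3 WEMWBS contrast, at 0.0498 in the final analysis, is the only unconditional confirmatory test.
2. If it is significant, test a short pre-specified sequence at the same level, stopping at the first non-significant result. The order should follow the Background, which expects well-being to improve quality of life and then physical health: for example the M0 to M3 change in EQ-5D (saying whether this is the questionnaire score or the VAS), then the M0 to M3 change in CESAM score.
3. Report every other secondary contrast as exploratory, with estimates and 95% confidence intervals.
4. Show all outcomes in the forest plots, whether or not they are significant.
5. Tie any claim of demonstrated physical-health benefit to success on the CESAM step.

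This costs a few sentences and needs no new data or participants. The downside is that an isolated secondary result with p < 0.05 can no longer be presented as a confirmed benefit, and a null EQ-5D result would stop the confirmatory test of frailty.

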#### Randomization

After the baseline assessment, participants are randomly allocated to intervention and control groups using block randomization with a 1:1 ratio. The randomization list is established with the N’Query randomization software by the project manager, who is the only person able to identify participants based on their code. All investigators are blind to randomization. The project manager is not involved in the recruitment nor the follow-up of participants. He conducts the randomization process and informs the participants of to which group they are assigned. Randomization is performed the week before the first workshop.

Furthermore, a subset of participants is offered a Fitbit Alta HR (Fitbit, Inc.; San Francisco, CA, USA) to record physiological measures (i.e., heart rate, daily step count, sleep duration, and its phases). The subset is limited to 30 intervention group and 30 control group participants, determined in a second randomization that keeps the subsets as similar as possible to control for selection bias. This second randomization adopts the process used during the first randomization and the same project manager oversees it to ensure that all investigators remain blind. After the second randomization is completed, the project manager in charge of randomization provides selected participants with a Fitbit device, an assessment schedule and instructions. The project manager also installs the Fitbit application on participants’ portable electronic devices and creates their individual accounts with coded usernames.

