### Power calculation

The number of participants required for this study has been calculated to detect the expected change in WEMWBS score between the baseline assessment (M0) and the end of the 3-month cycle (M3) calculated using the formula ((score M^*n* + 1^ – score M^*n*^)/((score M^*n* + 1^ + score M^*n*^)/2)) × 100. The expected difference between intervention and control group was estimated 5.2 ± 10.3 based on a previous study [21]. A free sample size calculator (http://www.sample-size.net/sample-size-means/) was used*.* The minimum number of participants to show an absolute difference between the 2 groups (i.e., intervention and control groups) with alpha = 5% and power = 90% is of 63 per group. Thus, the theoretical total number of participants for the study is 126. Anticipating an 18% rate of participant loss during the follow-up period, the total number of participants required is 150 (75 participants per group).

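### Baseline WEMWBS is not a covariate in the primary comparison or in the adjusted model; the estimate stays unbiased, but precision is given away

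*Protocol article*

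**What the plan says.** The Outcomes section defines the endpoint: "The primary outcome is the change in WEMWBS score between the baseline assessment (M0) and the end of the 3-month cycle (M3"). The change is symmetrised, that is, divided by the mean of the two scores and multiplied by 100.

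Under Data analysis, group comparisons of these changes "will be performed using repeated measures tests as appropriate". No covariate is named, and the protocol itself calls this step univariate. A multivariate analysis follows, "to determine the effect of the intervention while adjusting for age, sex, number of medications taken daily, and CPQ score". The protocol justifies these four variables as possible influences on the relation between outcome and intervention. Baseline WEMWBS is not among them.

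The score is available. The Baseline assessment section has WEMWBS taken from all participants in both arms at the first meeting, and the Randomization section places allocation after that assessment, "using block randomization with a 1:1 ratio". No stratification by baseline well-being is described.

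**The concern.** Change from baseline usually correlates negatively with baseline: people who start low tend to rise and people who start high tend to fall, whatever their arm. Dividing by the mean of the two scores does not remove this. A comparison of changes that ignores baseline therefore carries variation that the trial has already measured and could take out. It also leaves any chance difference in starting well-being to pass into the estimate. On the raw scale the regression slope of change on baseline is −(1−r), so a baseline difference of D between arms shifts the observed difference in change by about −(1−r)D.

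Power is at stake. On the protocol's own inputs, 63 per group gives about 80% power and not the stated 90%, so even a modest gain in precision is useful.

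**Working it through.** **Inputs from the protocol.** Difference and SD: "The expected difference between intervention and control group was estimated 5.2 ± 10.3 based on a previous study". Error rates and size: "with alpha = 5% and power = 90% is of 63 per group". Sidedness: "The global significance limit will be set at 0.05 and all tests will be bilateral". At the final analysis the protocol "will consider the value *p* < 0.0498 as significant"; using 0.0498 in place of 0.05 changes the power below by less than 0.1 point.

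**Assumed, not in the protocol.** The correlation r between M0 and M3 WEMWBS, and equal variances at the two times.

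**Step 1: the plan's own figure.** n per group = 2(z₁₋α/₂ + z₁₋β)²(SD/δ)², with (10.3/5.2)² = 3.923.
- 90% power: 2 × (1.960 + 1.282)² × 3.923 = 82.5, so 83 (84 by the t test).
- 80% power: 2 × (1.960 + 0.842)² × 3.923 = 61.6, so 62 (63 by the t test).

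The stated 63 is therefore the 80% figure. Directly, SE = 10.3 × √(2/63) = 1.835; 5.2/1.835 − 1.960 = 0.873; power = Φ(0.873) = 80.9% (80.3% by noncentral t).

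**Step 2: effect of adjusting for baseline.** With common variance s²:
- Var(change) = 2(1−r)s²
- Cov(change, baseline) = −(1−r)s²
- Squared correlation of change with baseline = (1−r)²/[2(1−r)] = (1−r)/2
- Residual variance after adjustment = change variance × (1+r)/2

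**Step 3: does this hold on the protocol's percentage scale?** WEMWBS was simulated as rounded scores limited to 14–70, with an assumed mean of 50 and SD of 7, 8 or 9, and 400,000 draws per setting. The symmetrised percent change was then regressed on baseline. Residual factors were 0.753–0.755 (r = 0.5), 0.800–0.807 (0.6), 0.849–0.852 (0.7), 0.902 (0.8) and 0.950–0.953 (0.9), against 0.75, 0.80, 0.85, 0.90 and 0.95 from the formula. Correlations of change with baseline ran from −0.22 to −0.50.

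**Step 4: power at 63 per group.** The adjusted SD is 10.3 × √((1+r)/2). For r = 0.7: 10.3 × √0.85 = 9.50; SE = 9.50 × √(2/63) = 1.692; 5.2/1.692 − 1.960 = 1.113; power = 86.7%.

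| r (assumed) | variance factor | SD | power, normal | power, t | n per group for 90% |
|---|---|---|---|---|---|
| unadjusted | 1.00 | 10.30 | 80.9% | 80.3% | 83 |
| 0.5 | 0.75 | 8.92 | 90.5% | 90.1% | 62 |
| 0.6 | 0.80 | 9.21 | 88.6% | 88.2% | 66 |
| 0.7 | 0.85 | 9.50 | 86.7% | 86.2% | 71 |
| 0.8 | 0.90 | 9.77 | 84.8% | 84.2% | 75 |
| 0.9 | 0.95 | 10.04 | 82.8% | 82.2% | 79 |

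The last column uses the normal approximation.

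**Step 5: which r is plausible?** The SD of 10.3 sets a rough limit. If baseline WEMWBS has coefficient of variation CV, then r ≈ 1 − (0.103/CV)²/2. An assumed CV of 0.12 gives r ≈ 0.63 and a CV of 0.20 gives r ≈ 0.87. The variance saving (1−r)/2 is then 18% to 7%, and power at 63 per group is about 88% to 83%.

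**The case against.** The strongest reply is that nothing here is an error. In a randomised trial a comparison of change scores is unbiased and the test is valid, so leaving baseline out is a choice about efficiency. That is correct. A reader might infer that the effect estimate is biased, and the documents do not support this: allocation is random, and chance imbalance is already reflected in the standard error.

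A reader might also infer that baseline is ignored altogether. It is not, since it enters both the numerator and the denominator of the change formula. Only its use as a covariate is missing.

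A third tempting reading is that adjustment restores the stated 90% power. That needs r of about 0.5 or lower. The protocol gives no r, and the rough range in Step 5 lies above 0.5. Nor does the protocol show that baseline is the strongest predictor of change; under the formula it explains 15% of the change variance at r = 0.7 and 5% at r = 0.9.

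Could the matter simply be left to an analysis plan? The open wording about the repeated measures test might be, but the adjusted model has a named and justified covariate list that includes computer proficiency and omits the outcome's own baseline. The protocol has fixed that choice. Nor does a repeated measures test bring baseline in by itself, because the values it compares are already changes from M0.

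**Conclusion.** The point holds as a loss of precision. Baseline WEMWBS is a covariate in neither analysis, though it is measured in everyone before allocation. Adding it would raise power at 63 per group by roughly 2 to 10 points from about 80%, for r from 0.9 down to 0.5.

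The omission of the covariate is certain from the text; the size of the benefit is not. It rests on an assumed r, on equal variances at M0 and M3, and on a two-group comparison at M3 as in the protocol's power calculation. It takes no account of variance that the four listed covariates may already explain. The sample-size shortfall is a separate matter, and baseline adjustment should not be presented as a full remedy for it.

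**What to change.** Keep the M0–M3 symmetrised percent change as the primary outcome. Analyse it with a linear model on arm, with the pre-randomisation M0 WEMWBS score as covariate, and add that score to the four covariates of the adjusted model. Do not leave modelling the M3 score as an open alternative: it reports scale points instead of percentages, and the 5.2 ± 10.3 planning figures would no longer apply directly.

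State which M0 value is meant. The Follow-up assessments section describes home questionnaires in the week before the first workshop, the same week as randomisation, and a further WEMWBS at the museum before that workshop in the intervention arm. These may follow knowledge of allocation. The covariate should be the score from the baseline interview before randomisation.

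Treat each secondary outcome in the same way, with its own pre-randomisation baseline. The activity-tracker measures need a separate statement, because the devices are handed out after allocation.

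The change needs no new data, visits or participants. Because recruitment has begun and an interim test of the primary outcome is planned at 90 participants, it should be recorded in a dated amendment before any unblinded look at the data.

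### The forest plot meant to rank outcomes by effect admits only significant ones, in percent units that depend on each scale's origin, so the effects it shows are overstated on average and its ranking is unsound

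*Protocol article*

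**What the plan says.** The third analysis step in the protocol article (Data analysis) has the stated aim "to identify the outcomes with the highest magnitudes of change (i.e., greater effect attributable to the intervention"). Its inclusion rule is "we will graph the mean difference of each outcome that is significantly different when comparing intervention group participants to those in the control group", and its format is given as "Results will be presented as forest plots".

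The plot sentence does not name its units. The preceding paragraph of Data analysis defines change as the difference between two scores divided by their mean, times 100. The Outcomes section adds "All changes will be expressed in percentages as mean values and standard deviations". No standardisation across scales is mentioned.

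On significance, Data analysis says "The global significance limit will be set at 0.05 and all tests will be bilateral"; the final primary analysis "will consider the value *p* < 0.0498 as significant (Haybittle-Peto method").

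The Baseline assessment section gives the scale ranges: WEMWBS 14 to 70, CESAM 0 to 18, EQ-5D VAS 0 to 100, and an EQ-5D total stated as 0 to 25, although five items coded 1 to 5 sum to 5 to 25.

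**The concern.** A display that ranks effects needs unbiased estimates on a common scale. This one has neither.

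- **Selection.** An estimate that must clear a significance threshold to be shown is, on average, larger than the truth. The excess is greatest where the true effect is smallest, so weak and strong outcomes look alike.
- **Units.** A percent of the score level is not comparable between a scale that starts at 14 and one that starts at 0. An outcome whose scores lie near zero can top the ranking without benefiting more.

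At stake is the trial's statement of which aspects of health gain most. The Discussion presents an effect on physical health, measured here by CESAM frailty, as the claim still to be validated, and CESAM is the questionnaire whose percent changes are most distorted by low scores.

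**Working it through.** **Inputs.** Power calculation: "The expected difference between intervention and control group was estimated 5.2 ± 10.3 based on a previous study", and "with alpha = 5% and power = 90% is of 63 per group"; 75 per group are randomised. Randomization: 30 per group in the Fitbit subset. Data analysis: two-sided 0.05, so the critical value c is 1.96 (using 0.0498 for the primary outcome makes no visible difference).

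**The plan's own figure.** The plot has no stated figure; the nearest is the sample size. n per group = 2(1.96 + z)² × (10.3/5.2)². At 90% power (z = 1.282) this gives 83; at 80% power (z = 0.842) it gives 62 (63 with the t distribution). So 63 per group has about 80% power, not 90%. That is a separate matter; 63 and 75 are used below only to set the standard error.

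**Selection on significance.** SE = SD × √(2/n).
- n = 63: SE = 10.3 × √(2/63) = 1.835, so only an observed difference of at least 1.96 × 1.835 = 3.60 is plotted.
- n = 75: SE = 10.3 × √(2/75) = 1.682, threshold 3.30.

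With θ = true difference/SE, the mean plotted size is about SE × [θ + φ(c − θ)/Φ(θ − c)]; the wrong-direction tail is included in the table. For a true 5.2 at n = 63: θ = 2.834, φ(−0.874) = 0.272, Φ(0.874) = 0.809, giving 1.835 × (2.834 + 0.337) = 5.82.

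| True difference | Chance of being plotted (n = 63) | Mean size plotted (n = 63) | Ratio | Mean size plotted (n = 75) | Ratio |
|---|---|---|---|---|---|
| 5.2 | 0.81 | 5.8 | 1.12 | 5.6 | 1.08 |
| 3.9 | 0.57 | 5.2 | 1.33 | 4.9 | 1.25 |
| 2.6 | 0.29 | 4.8 | 1.83 | 4.4 | 1.70 |
| 1.3 | 0.11 | 4.5 | 3.4 | 4.1 | 3.2 |

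At 63 per group a fourfold range of true effects (5.2/1.3) is displayed as a 1.3-fold range (5.8/4.5). The ratio depends only on difference/SD, so it carries over to any continuous outcome with the same standardised effect. In the Fitbit subset the threshold is 1.96 × √(2/30) = 0.51 SD. Assumed true effects of 0.5 and 0.3 SD would be shown on average as 0.71 (×1.42) and 0.65 (×2.2).

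**Dependence on origin.** Percent change = 200 × (b − a)/(b + a), with a the earlier and b the later score. A fall of one CESAM point:
- 10 to 9: 200 × 1/19 = 10.5%
- 2 to 1: 200 × 1/3 = 66.7%
- 1 to 0: 200 × 1/1 = 200%
- no change, 0 to 0: 0/0, undefined

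The vigorous category is 0 to 3, so these low scores are within the expected range. As a share of the scale, one point is always 1/18 = 5.6%.

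The other scales behave alike (illustrative scores). WEMWBS 50 to 52.5 is 200 × 2.5/102.5 = 4.9%; scored from 0 instead of 14 (36 to 38.5) it is 200 × 2.5/74.5 = 6.7%. An EQ-5D total going from 7 to 6 is 200 × 1/13 = 15.4%; scored from 0 instead of 5 (2 to 1) it is 66.7%.

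**Same benefit, different rank.** The documents give no baseline means or SDs for these scales, so assume WEMWBS 50/8, CESAM 3.5/2.5, EQ-5D total 7/2 and VAS 80/12. Apply an improvement of 0.3 SD to each mean:
- WEMWBS: 200 × 2.4/102.4 = 4.7%
- CESAM: 200 × 0.75/6.25 = 24%
- EQ-5D total: 200 × 0.6/13.4 = 9.0%
- VAS: 200 × 3.6/163.6 = 4.4%

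With the CESAM mean varied from 2 to 6, its figure runs from 200 × 0.75/3.25 = 46% to 200 × 0.75/11.25 = 13%. CESAM ranks first throughout, although the standardised benefit is identical.

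**The case against.** The strongest reply is that this is one descriptive figure, the third step of the analysis. The step before it compares the groups on changes at every visit with no significance filter, and the Outcomes section pre-specifies all secondary outcomes. That stands, and it limits the point to this display and its ranking.

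Three stronger readings are tempting and are not supported.

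- **That the plan hides harm.** The tests are two-sided and the filter is significance, not direction, so a significantly adverse effect would be plotted. What the figure leaves out is non-significant results in either direction.
- **That the plan reports selectively.** Nothing says that results absent from the figure go unreported.
- **That many plotted outcomes would be chance findings.** Counting every secondary outcome at every visit gives at least 56 comparisons and 56 × 0.05 = 2.8 expected by chance. But 25 of these are frailty categories (5) or service use (20), which do not yield a mean difference. The rest are WEMWBS 4, CESAM score 5, EQ-5D 5, VAS 5 and Fitbit 12: 31 comparisons, 31 × 0.05 = about 1.6. Even that assumes a separate test at each visit and no effect anywhere; the planned repeated measures tests may be fewer.

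It is also fair that power is documented only for the primary outcome, so the ratios for smaller effects rest on assumed true differences. And the plot sentence says only mean difference, so percent units are inferred. If raw scores were meant, the origin problem goes, but points on a 0 to 18 scale and points on a 0 to 100 scale still cannot be ranked together.

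**Conclusion.** The point holds for this figure. Followed as written, the plan shows estimates that are overstated on average: by about 8% to 12% at the planned difference of 5.2, and by more for weaker outcomes and in the 30-per-group subset. This assumes SD 10.3, 63 to 75 per group, a normal approximation and a two-sided 0.05 filter. If the global significance limit means a stricter threshold per outcome, fewer chance findings enter but the overstatement of those shown increases.

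The ranking is unsound on either reading of the units. In percent it depends on each scale's origin and is undefined for a participant scoring 0 on CESAM at both visits; in raw points the scales are not comparable. The primary comparison, sample size and stopping rule are untouched. The plan should be changed here, but the trial's main conclusion does not depend on it.

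**What to change.** Replace the third step of Data analysis with a display that does not filter on significance:

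- Plot all pre-specified outcomes whatever their p value, each with a 95% confidence interval.
- Show continuous outcomes (WEMWBS, CESAM score, EQ-5D score, VAS, Fitbit measures) as standardised mean differences: the between-group difference in raw-score change divided by the pooled baseline SD. Align signs so that benefit points the same way, since higher CESAM and EQ-5D totals are worse.
- Show frailty categories and service use in a separate panel as risk or rate differences or ratios; a standardised mean difference does not suit them.
- Mark the primary outcome and label the secondary outcomes exploratory.

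The cost is a larger figure and a second panel. No new data are needed, and no test changes.
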